**Treatment services and adverse events**				
Program and client costs (PACC-SAT) [126–128]	Treatment utilization and cost, mediator	X	X	
Adverse events (SAFTEE) [129]	Safety outcome		X	X

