**Implementation-related measures**				
Cost-related data	Cost effectiveness	X	X	X
Participant satisfaction	Evaluation		X^a^	X^a,c^

^a^Indicates participant self-administered via survey

^b^Verified with objective measures at follow-up for outcome ascertainment [55, 131]

^c^Completed at 90 day assessment only if not completed at 34 day assessment

A secondary outcome of AUD treatment engagement is potential change in use and cost of health services from before the index hospitalization to a comparable period following hospital discharge. Reduction in health service use and costs would be a cost-savings outcome (i.e., benefit of the intervention) [58]. Even if these health service use and cost savings do not completely compensate for intervention costs, they could at least reduce net intervention cost. Emergency department, outpatient, and inpatient visits as well as medication before and after hospitalization will be extracted from the electronic health record for the 12 months before and following hospitalization. Intervention costs themselves will be assessed by multiplying provider and patient time spent for each patient in each intervention condition by provider and patient self-reported wage rates including employment perquisites, plus any materials, medication, and other resources used in interventions. These costs, and costs of computers and software used in CBT4CBT conditions will be assessed using methods developed in previous research published by several of the current authors [58].

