Intervention-level cost per engaged patient will be calculated, along with increments in this cost as successive interventions are added. We will conduct analyses to determine the type, amount, and monetary values (i.e., costs) of the major resources used to implement each intervention for each patient, including time of professionals and patients, medication, and other intervention materials and resources. Combining cost with effectiveness data for individual patients will make possible descriptive scattergrams and group-level graphs of effectiveness = *f* [costs] and benefits = *f*[costs] as well as statistical analyses comparing effectiveness/cost ratios (e.g., change in PHDD per $100 of resources consumed by intervention) and other indices of relationships between costs and effectiveness for patients in each intervention condition. Average and median effectiveness/cost will be compared statistically for each condition with individual-level effectiveness and costs [58]. Cost per effectively treated patient also will be calculated at the group level, defining effective treatment according to quantitative definitions of clinically meaningful change in alcohol use. Similar analyses will examine graphically and statistically cost–benefit relationships as expressed by individual-level net benefit (i.e., reduction following intervention in costs of ED and readmission minus costs of intervention) [58]. Further, building on a mixed-methods evaluation that informed the study protocol [44], we will conduct a survey of hospital-based clinicians and staff upon conclusion of the clinical trial regarding their perspectives on the alcohol treatment interventions and necessary supports to sustain delivery of these interventions outside of the research infrastructure. We will also capture factors that may contribute to inequitable care among historically minoritized racial and ethnic groups.

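### The net-benefit formula is narrower than the plan's own definition of benefit and leaves post-discharge outpatient AUD treatment out of both of its terms

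*Protocol article*

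**What the plan says.** The Implementation-focused process evaluation section of the protocol article gives the formula for the cost–benefit analysis: "individual-level net benefit (i.e., reduction following intervention in costs of ED and readmission minus costs of intervention". The same section lists what goes into the cost of each intervention, "including time of professionals and patients, medication, and other intervention materials and resources".

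The Data collection protocol section, in the text after Table 2, describes benefit more widely: "Reduction in health service use and costs would be a cost-savings outcome (i.e., benefit of the intervention". It also names the data to be drawn from the electronic health record for the 12 months before and the 12 months after hospitalization: "Emergency department, outpatient, and inpatient visits as well as medication before and after hospitalization will be extracted". Intervention cost is described there as provider and patient time valued at wage rates, "plus any materials, medication, and other resources used in interventions".

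Table 2 also lists a program-and-client cost instrument, with the stated purpose "Treatment utilization and cost, mediator", at baseline and 34 days.

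**The concern.** The two sections define benefit differently. One covers health service use and cost in general; the other covers only ED visits and readmissions. The difference matters because of what falls between them. All arms are referred to formal AUD treatment, and the primary outcome is whether participants engage in it. The outpatient part of that treatment is neither an ED visit nor a readmission. It is also not a resource used to deliver the intervention, so it does not belong to intervention cost as described.

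Used as written, the formula credits an arm with any acute-care cost that treatment averts but does not charge the outpatient treatment that averted it. The omission need not be equal across arms, because it depends on how many participants engage. Cost–benefit comparison of the three arms is a declared part of Aim 3, and the Discussion offers it as guidance for other health systems.

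**Working it through.** The plan states no net-benefit figure, unit cost or standard deviation, so there is no figure to reproduce. The check is one of definitions, followed by algebra with an assumed cost.

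**Step 1: where each cost falls.**

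| Cost | Wider definition (Data collection protocol) | Net-benefit formula (Implementation-focused process evaluation) |
|---|---|---|
| ED visits, readmissions | counted | counted |
| Outpatient visits, including AUD treatment | extracted; part of service cost | in neither term |
| Medication used in the interventions | charged as intervention cost | charged as intervention cost |
| Medication continued after discharge | extracted | unclear |
| Staff and patient time, materials | intervention cost | intervention cost |

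The unclear entry arises because the Facilitated provision of MAUD section has the medical team prescribe through ordinary channels. The article does not say whether later supply counts as an intervention resource or as a health service cost.

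**Step 2: the omitted amount.** For each participant let R be the fall in ED and readmission cost, I the intervention cost, and O the net rise in outpatient cost.

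- Formula as written: R − I
- Formula over all extracted services: R − O − I
- Difference: O

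Let C be the net extra outpatient cost per engaged patient: the treatment cost less any fall in other outpatient cost. Take it as zero for those not engaged. Between two arms the mean of O then differs by (engagement difference) × C.

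**Step 3: inputs.** The Justification of sample size section assumes 40% engagement with BNI and plans for an increase of 15, read here as percentage points (40% to 55%). It uses 20 points for the 360-participant case. C is not in the documents; $500 to $5,000 is an assumption.

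| Assumed C | 15 points: 0.15 × C | 20 points: 0.20 × C |
|---|---|---|
| $500 | $75 | $100 |
| $1,000 | $150 | $200 |
| $2,500 | $375 | $500 |
| $5,000 | $750 | $1,000 |

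These are overstatements of net benefit per randomized participant, relative to the less engaging arm.

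**Step 4: can the conclusion change?** Suppose, purely for illustration, that an arm saves $400 in ED and readmission cost against BNI and costs $200 more to deliver. The formula as written gives 400 − 200 = +$200. With outpatient cost charged at a 15-point gain:

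- C = $500: 200 − 75 = +$125
- C = $1,000: 200 − 150 = +$50
- C = 200 / 0.15, about $1,333: zero
- C = $2,500: 200 − 375 = −$175
- C = $5,000: 200 − 750 = −$550

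The sign depends entirely on assumed values. If C is zero because lower drinking reduces other outpatient use by as much as treatment adds, nothing is overstated. If C is negative, the formula understates benefit.

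**The case against.** The strongest reply is that the plan does not ignore these costs. Outpatient visits and medication are extracted, an instrument for treatment use and cost is scheduled, and the wider definition of benefit already includes them. That stands. A reader might infer from the formula that treatment and medication are never charged anywhere. The documents do not support this: medication used in the interventions is named as an intervention cost in both sections, and outpatient care is collected and lies within one of the two definitions. The defect is confined to one formula that drops it.

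A second reply is that the article is condensed and refers its costing method to earlier published work, so the full component list may be set elsewhere. That lowers confidence about what will be done. It does not reconcile two definitions printed in the same article, and the narrower one is worded as a definition, not as an example.

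Third, the direction of bias is conditional. It requires engagement to rise across arms as hypothesized and the added treatment cost not to be offset by falls in other outpatient cost. This stands. A reader might also infer that a cost-increasing arm would be reported as having a positive net benefit. That is possible but not shown, because every unit cost in the illustration is assumed and the sign holds at $500 and at $1,000.

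Fourth, the formula defines net benefit only, not the numerator of the benefit/cost ratios. That is correct, and it leaves open which of the two definitions the ratios will use.

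Finally, this is one Aim 3 index among several, alongside cost per engaged patient, effectiveness/cost ratios and incremental cost-effectiveness ratios. That limits the weight of the point without removing it.

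**Conclusion.** The point holds as an inconsistency with a likely differential effect. The net-benefit formula is narrower than the plan's own definition of benefit, and post-discharge outpatient AUD treatment falls in neither of its terms. Given the hypothesized ordering of engagement and a positive net outpatient cost per engaged patient, net benefit is overstated for the more engaging arm. At the planned 15-point difference the overstatement is $75 to $750 per participant for an assumed $500 to $5,000. Neither that size nor a change of sign can be established from the documents. The point concerns Aim 3 only; the primary outcome is untouched. It should be corrected before the cost–benefit analysis is run.

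**What to change.** In the Implementation-focused process evaluation section, define net benefit as the fall in the total of all service costs that the Data collection protocol section extracts, minus intervention cost. That total comprises ED, inpatient, outpatient including AUD treatment, and medication. State whether medication continued after discharge belongs to intervention cost or to service cost, so that each drug is counted once. Use the same definition of benefit in the benefit/cost ratios. Keep the ED-plus-readmission version as a labelled component or a sensitivity analysis.

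For AUD treatment received outside the health system, include the cost only where the quantity of use is recorded, and otherwise state the limitation. The article describes verifying engagement and classifying treatment type by the ASAM criteria, but does not say that visit counts or duration are obtained. Type alone does not give quantity.

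The cost is a change of wording and the unit-costing of data already planned for extraction. The total will be somewhat noisier, and net benefit will probably look less favourable.

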#### Ethical approval and protection of participants

This HIPAA-complaint study is approved by the Yale School of Medicine Human Investigation Committee (protocol #2000031874). The Data Safety and Monitoring Board will review enrollment, baseline characteristics of enrolled participants, intervention delivery, adverse events, and outcome ascertainment biannually starting approximately 6 months after enrollment initiation.

#### Current status of *Project ENHANCE*

In preparation for study launch, the *Project ENHANCE* team engaged a variety of hospital and university-based stakeholders to refine study processes and prepare for implementation. This led to the development of a multi-pronged approach to inform recruitment strategies. In addition, based on these discussions, the *Project ENHANCE* team offered a set of four 1-h conferences to hospitalist-based clinicians regarding the importance of providing alcohol treatment in the hospital setting, treatment options, unique factors impacting minoritized racialized and ethnic populations, and the study protocol with an emphasis on CBT4CBT. Continuing medical education credits (CME) were offered for attendance with the goal of providing basic education regarding the importance of addressing AUD in the hospital setting; considerations for providing care through an equity lens; considerations for prescribing MAUD among medically complex patients; and the evidence for CBT4CBT.

After completion of this series and trainings of study staff, *Project ENHANCE* opened for recruitment on September 13, 2022, and recruitment and follow-up are ongoing.

## Discussion

*Project ENHANCE* will generate novel data on the comparative effectiveness of three different treatment strategies on promoting AUD treatment engagement and alcohol reduction post-hospital discharge among a diverse sample of patients with untreated AUD, with special emphasis on minoritized racial and ethnic patients. Our protocol is timely and highly relevant for several reasons. First, few prior studies have focused on the hospital setting to reach individuals with untreated AUD, though one important study focused on evaluating different formulations on naltrexone [14]. We build on this work by evaluating an intervention that is flexible with regards to the specific type and formulation of MAUD with ultimate prescribing at the discretion of the participant and primary team. Second, although there have been studies using digital interventions to address alcohol use in outpatient and emergency settings [96–98], to our knowledge, no studies have sought to initiate a robust digital treatment intervention to address AUD or any other substance use disorder in the inpatient hospital setting. Our trial will be amongst the first to evaluate the impact of the evidence-based CBT4CBT platform on AUD treatment engagement when initiated in the hospital setting [12, 26]. Third, our team’s diverse perspectives and expertise is unified by a commitment to promote health equity and address the role of structural racism as a driver of AUD and its consequences, as well as a barrier to treatment. We expect to generate new insights on the prevalence and correlates of SDOH among our sample of enrolled participants and the moderating effect of SDOH on intervention effects and outcomes, expanding beyond traditional measures of SDOH (e.g., housing status) [5]. Fourth, there is significant interest in complementing self-reported alcohol use with an alcohol biomarker, such as PEth [38], yet there have been few studies that collected PEth in the hospital setting. We anticipate examining the correlation between self-reported alcohol use and the biomarker PEth among patients experiencing acute illness and across clinically relevant subgroups [99] and its association with clinical measures over time (e.g., cognitive function). Lastly, given the hybrid type 1 effectiveness-implementation design, we hope to generate critical data including cost, cost-effectiveness, and cost–benefit, useful for informing future implementation of these different HPA-delivered treatment strategies in other large, urban health systems in diverse communities.

### Limitations

We expect limitations to our study. First, our focus has been to address the role of race and ethnicity in all aspects of study design and implementation; however, we have not had a similar focus on the role of gender that should be considered in future work. Second, while the MAUD conditions intend to facilitate MAUD through provision of patient and clinician facing materials, this may not be sufficient to stimulate actual prescribing. Third, the ongoing challenges of the COVID-19 pandemic have had a significant impact on clinicians, including burnout; clinicians may be less motivated, prepared, and able to address AUD in these circumstances. Fourth, Addiction Medicine Consult Services are increasingly available in hospitals across the United States, yet this still represents the minority of hospitals. In addition, the study is being conducted in an academic hospital system in New Haven, CT, which offers a range of accessible services for AUD upon hospital discharge. Thus, findings may not be generalizable to contexts where AUD treatment services are not as robust, including community hospitals and other regions of the United States. Fifth, all participant-facing documents and the CBT4CBT platform are available in English and Spanish and our team’s Research Coordinators are all fluent in English and Spanish. However, consistent with common practice at YNHH, interventions delivered by the HPAs will require use of translation services for Spanish-only speaking patients due to the skills of our current team members. Lastly, due to resource constraints, research coordinators and the HPAs will not be blinded to study conditions; no team member, however, will have a priori knowledge about group assignment prior to randomization.

## Conclusion

*Project ENHANCE* is expected to generate timely data to inform hospital-based practices on equitable strategies for promoting AUD treatment engagement and alcohol reduction among patients with untreated AUD to mitigate AUD-related morbidity and mortality.

## Data Availability

Datasets generated during the current study will be made available from the authors upon request and be made publicly available in a deidentified format consistent with NIAAA policies to the National Institute of Mental Health Data Archive repository.
